#### Sample analysed

Because this is a study of effectiveness, the main analysis will be carried out following intention to treat principles. The safety analysis will be carried out on all participants who received at least one injection, whatever the substance injected. For the safety analysis, participants will not be analysed according to treatment allocation, but according to the treatment actually received.

#### Missing, unused or invalid data

The status of the patients (included, randomised, evaluated as intention to treat, lost to follow-up, left the study or deviated from the protocol) will be described and compared for each treatment arm and centre. Patients lost to follow-up, deceased (which should be exceptional) or left the study will be censored at the date of the last information. In case of censure, the last known value of the result will be used. All missing or invalid data will be replaced by the last available data for the corresponding parameters for the patient. The “last observation carried forwards procedure” will be used. In case of a large quantity of missing data, sensitivity analysis using conditional imputation will be carried out.

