## Background

Around 85% of stroke survivors regain the capacity to walk. However the kinetic and kinematic parameters of post-stroke gait are typically altered, with a reduction in cadence, stride length and velocity [1–3]. Stiff knee gait (SKG), characterized by decreased knee flexion during swing phase [4], and equinus (reduced ankle dorsiflexion) [5] are common post-stroke gait patterns.

The loss of knee flexion during swing can be attributed to several mechanisms, including weakness of the hip flexor muscles, a reduced plantar flexion moment and inappropriate activity of part of the quadriceps muscle, particularly the Rectus Femoris (RF) [4]. The bi-articular RF is normally active during the final phase of double support (end of stance, beginning of swing) to control knee flexion. If it is inappropriately activated during swing, it restricts knee flexion during this phase [4, 6, 7].

The loss of dorsiflexion can be secondary either to weakness of the dorsiflexor muscles, particularly the Tibialis anterior (TA), or to inappropriate activity of the Triceps Surae (TS) muscles [8, 9]. Inappropriate activity of the TS reduces dorsiflexion and results in initial contact with the foot in plantar flexion.

Medical interventions to improve gait mostly target the inappropriate activity of the RF and TS. Botulinum toxin type A (BTX-A) is a common treatment to reduce muscle activity. It blocks the liberation of neurotransmitters at the presynaptic neuromuscular junction, inducing focal, transitory and reversible paralysis of the injected muscle. The effect lasts around 3 months [10].

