### Study design

The study will be prospective, 3-centre, randomised, placebo-controlled and triple blinded. The total duration of the study will be 36 months. The duration of participation of each patient will be 3 months, with four visits. The patients and the injecting doctors and assistants, as well as the evaluators will be blinded to the patients’ group allocations. Randomization will be carried out by computer software. During visits V1, V3 and V4 the measurements will be carried out throughout the day with breaks allowed between each (Table 1).

**Table 1 Tab1:** Tests and evaluations during each visit

Tests and evaluations	V1	V2	V3	V4
Inclusion/ exclusion criteria	X			
Informed consent	X			
Randomisation	X			
Injection BTX-A or placebo		X		
Evaluation of passive range of motion (MG)	X		X	X
Evaluation of spasticity (MAS)	X		X	X
Evaluation of strength (MRS)	X		X	X
SF 36	X		X	X
FIM	X		X	X
ABILOCO scale	X		X	X
Berg balance scale	X		X	X
Abc scale	X		X	X
Timed up and go	X		X	X
3D analysis	X		X	X
Isokinetic evaluation	X		X	X

*V1* visit 1, *V2* visit 2, *V3* visit 3, *V4* visit 4, *MA* manual goniometer, *MAS* modified Ashworth, *MRC* Medical Research Council, *SF36* The Short Form (36) Health Survey, *FIM* Functional independence measure, *3D analysis* gait motion analysis. All outcome measures will be evaluated during the first visit (baseline-V1) and 1 month (V3) and 3 (V4) months after injection. All evaluations will be performed in the same order at each session in order to limit bias related to fatigue

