#### Analysis of primary outcome

Change in peak length of the RF and TS muscles during gait at 1 month (difference in length between V3 and V1 will be compared between groups using a Student t-test. To prevent the risk of false positives induced by multiple testing, a Bonferroni Holm correction will be applied to the *p*-values for peak length, peak force and peak strength [61]. The level of significance will be set at 0.05/3.

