#### Analysis of secondary outcomes

The statistical test used for the primary outcome will also be used to evaluate the effect of BTX-A at 3 months (V4). To compare changes in the secondary criteria across visits between the two groups (change in peak length of injected muscles, joint angles, modified Ashworth score, functional scores and quality of life), repeated measures models will be used. Depending on the distribution of continuous or binary variables, mixed models or generalized estimation equations (GEE) will be used respectively. The models will include the treatment variable (BTX-A or placebo), time and interaction between time and treatment as explanatory factors. If a significant interaction is found, comparisons between both groups (BTX-A and placebo) will be carried out for each time-point using a Student t-test. In order to take in to account any effects of multiple testing, these outcomes will be considered as explanatory factors rather than determinants of the effectiveness of BTX-A.

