#### Management of changes to the planned analysis

Changes or supplementary analyses could be carried out. They will be considered as “post-hoc” and will be reported as such in the analysis and publication. Any retrospective changes to the planned analysis will be validated by the Study Committee and justified in an amendment to the protocol and in the trial report.

The statistical analysis will determine if BTX-A: i) increases peak muscle length during gait; ii) reduces peak force generated; iii) improves inter-segmental coordination during gait and iv) improves performance on functional tests.The second aim is to determine whether the effects of BTX-A are maintained at V4 compared with V1, suggesting a remnant action of BTX-A.

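### Carrying the last observation forward sets a missing 1-month change to exactly zero and biases the 3-month estimate in a direction that depends on when patients are lost

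*Protocol article*

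**What the plan says.** The rule is in the Protocol article, section Missing, unused or invalid data: "All missing or invalid data will be replaced by the last available data for the corresponding parameters for the patient". For patients who leave, "In case of censure, the last known value of the result will be used". The same section names the procedure as LOCF and offers one check on it: "In case of a large quantity of missing data, sensitivity analysis using conditional imputation will be carried out". No threshold for that quantity is given.

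The note to Table 1 (Study design) fixes the measurement times: "All outcome measures will be evaluated during the first visit (baseline-V1) and 1 month (V3) and 3 (V4) months after injection". V2 is the injection visit and has no outcome assessment.

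For the primary analysis (Analysis of primary outcome), the "difference in length between V3 and V1 will be compared between groups using a Student t-test". The section Analysis of secondary outcomes says for the later visit: "The statistical test used for the primary outcome will also be used to evaluate the effect of BTX-A at 3 months (V4"). The section Management of changes to the planned analysis says that this later comparison asks "whether the effects of BTX-A are maintained at V4 compared with V1".

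Two statements bear on the expected time course. The Background says of the toxin: "The effect lasts around 3 months". The Discussion expects the effect at 1 month and only possibly at 3 months, and expects no significant improvement on placebo.

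**The concern.** No outcome is recorded between V1 and V3, so the only value available to carry into V3 is the baseline. Every patient without a usable V3 is scored as having no change at all, whatever happened to the muscle. The rule covers invalid data as well as drop-out. A failed gait recording at V3 in a patient who returns at V4 would therefore also count as zero change.

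At V4 the carried value is the 1-month result for anyone seen at V3 but not at V4. That enters a 1-month response into a test of whether the response persists to 3 months. Anyone lost before V3 has the baseline carried to V4, which enters zero.

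The estimated size of the 1-month change and the answer on persistence are both at stake. Both would partly reflect the pattern of visit attendance.

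**Working it through.** **Inputs from the protocol article.** 17 per group, two-sided 5%, 80% power, 40 recruited (Sample size calculation); threshold 0.05/3 (Analysis of primary outcome); outcomes at V1, V3 and V4 only (Table 1); no placebo improvement expected (Discussion).

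**Inputs not given, so assumed.** Effect size, SD, loss rate and the share of the effect left at 3 months. Allocation is taken as 1:1, loss as unrelated to outcome, and SD of change as 1.

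**The plan's own figure.** 17 per group cannot be reproduced, because no effect size or SD is stated. Solving backwards with a two-sample t-test gives a standardised difference d between 0.991 and 1.024. d = 1.0 returns 17 per group and is used below. The implied allowance for loss is 1 - 34/40 = 15%.

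**V3, expected difference under LOCF.** With true mean changes dT and dP, and shares mT and mP missing V3:

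E[difference] = (1 - mT) × dT - (1 - mP) × dP

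| Scenario | Calculation | LOCF | True |
|---|---|---|---|
| Placebo 0, 15% missing in each arm | 0.85 × 1 | 0.85 | 1.00 |
| Placebo 0, 25% missing on BTX-A | 0.75 × 1 | 0.75 | 1.00 |
| Placebo 0, 5% missing on BTX-A | 0.95 × 1 | 0.95 | 1.00 |
| Changes 1.5 and 0.5; 5% and 25% missing | 0.95 × 1.5 - 0.75 × 0.5 | 1.05 | 1.00 |
| Changes 1.5 and 0.5; 25% and 5% missing | 0.75 × 1.5 - 0.95 × 0.5 | 0.65 | 1.00 |
| Changes 0.5 and 0.5; 5% and 25% missing | 0.95 × 0.5 - 0.75 × 0.5 | 0.10 | 0.00 |

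In each row the BTX-A figure comes first. In the last row the simulated type I error is 5.9%.

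**V3, power.** Simulation with 50,000 runs, 20 per arm, d = 1, placebo change 0, equal loss:

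| Missing V3 | 5% level: observed data / LOCF | 0.05/3 level: observed data / LOCF |
|---|---|---|
| 5% | 85.2% / 84.8% | 71.5% / 70.9% |
| 10% | 82.9% / 82.2% | 68.8% / 67.5% |
| 15% | 80.6% / 79.5% | 65.5% / 63.3% |
| 20% | 78.4% / 76.8% | 62.0% / 58.8% |

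**V4, expected difference under LOCF.** Let a be the share missing both V3 and V4, b the share missing V4 only, and d3 and d4 the true differences at the two visits. The same loss pattern is taken in both arms, or no placebo change.

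E[V4 difference] = (1 - a - b) × d4 + b × d3

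Bias = b × d3 - (a + b) × d4, which is upward only if d4/d3 < b/(a + b).

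With a + b = 15%, d3 = 1 and d4 = 0.30:

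- all lost after V3 (a = 0, b = 0.15): 0.85 × 0.30 + 0.15 = 0.405;
- even split (a = b = 0.075): 0.85 × 0.30 + 0.075 = 0.330;
- all lost before V3 (a = 0.15, b = 0): 0.85 × 0.30 = 0.255.

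The true value is 0.30 in all three. If the effect has gone entirely (d4 = 0), the estimate is 0.15, 0.075 and 0 respectively.

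**The case against.** The strongest reply is that the rule costs little. At the implied 15% loss, power on the primary test falls by about 1 point at the 5% level and about 2 at 0.05/3. If placebo patients do not change, the primary bias is conservative and cannot create a false claim of benefit. The 3-month comparison is secondary, and the plan says that secondary outcomes do not determine effectiveness. A sensitivity analysis by conditional imputation is also foreseen. All of this stands and limits the severity. It does not remove the bias in the estimate, and the sensitivity analysis depends on an amount of missing data that nobody has defined.

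A reader might infer three stronger things that the document does not support.

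- **That LOCF always inflates the 3-month effect.** It does so only when d4/d3 is below b/(a + b). Patients lost before V3 carry a zero into V4 and pull the estimate down.
- **That the full 15% loss distorts both visits in opposite directions.** The same drop-outs cannot leave both before and after V3, so the worst case at one visit excludes the worst case at the other.
- **That dilution at V3 is certain.** It needs equal loss or no placebo change. The protocol expects no placebo improvement, so dilution is the likely case, but with placebo change and unequal loss the bias can go either way.

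The protocol also does not say that the effect peaks at 1 month. Waning by V4 is inferred from the Background and the Discussion.

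**Conclusion.** The point holds, as something that should be fixed before unblinding. By construction, a missing or invalid V3 makes the primary change exactly 0. With equal loss or no placebo change, the expected 1-month difference is (1 - m) of the truth, or 85% at an assumed 15% missing.

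The 3-month estimate mixes carried-forward V3 and V1 values and is biased up or down according to when patients leave. With 15% loss and 30% of the effect retained, it would lie between 25.5% and 40.5% of the 1-month effect.

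The power cost on the primary test is about 1 to 3 points across 10% to 20% loss, and less at 5%. These sizes rest on assumptions: d of about 1, the loss rates, the retained fraction, and loss unrelated to outcome. That a missing V3 is scored as zero change rests on none of them.

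**What to change.** Replace LOCF as the main rule. Fit a likelihood-based repeated-measures model to the observed data that treats V1, V3 and V4 jointly as outcomes, with visit and treatment-by-visit terms. Take the V3 contrast as primary and the V4 contrast as secondary. Modelling V1 as an outcome means that every randomised patient with a baseline value contributes. With baseline only as a covariate, a patient with neither V3 nor V4 would drop out of the analysis.

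Always run a missing-data sensitivity analysis, for example multiple imputation based on the placebo arm, and delete the condition about a large quantity of missing data. Keep LOCF, if wanted, only as a labelled sensitivity analysis.

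The cost is a protocol amendment, for which the section Management of changes to the planned analysis already gives the route, and a little more analysis work. Mixed models are already planned for the secondary outcomes. The new main analysis assumes data missing at random, which cannot be verified. That is why the sensitivity analysis should not be optional.

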#### Management of changes to the planned analysis

Changes or supplementary analyses could be carried out. They will be considered as “post-hoc” and will be reported as such in the analysis and publication. Any retrospective changes to the planned analysis will be validated by the Study Committee and justified in an amendment to the protocol and in the trial report.

The statistical analysis will determine if BTX-A: i) increases peak muscle length during gait; ii) reduces peak force generated; iii) improves inter-segmental coordination during gait and iv) improves performance on functional tests.The second aim is to determine whether the effects of BTX-A are maintained at V4 compared with V1, suggesting a remnant action of BTX-A.

## Discussion

We expect that BTX-A injection in the RF and TS muscles will increase their length and peak lengthening velocity and decrease peak muscle force during gait 1 month, and perhaps also 3 months, after the injection. We expect to find a reduction in the spasticity of these muscles, an increase in passive knee flexion and passive ankle dorsiflexion, a decrease in knee extensor and plantarflexor muscle strength (MRC scale, and isokinetic dynamometer) and a reduction in force generated by these muscles during gait (SIMM model) in the BTX-A group. The peak force couple produced by the knee flexors/extensors during active movements (measured on the isokinetic dynamometer) should decrease, and the angle at which peak force occurs during passive movements should increase, demonstrating a decrease in spasticity. We also expect spatiotemporal gait parameters to improve, with an increase in gait velocity, cadence and stride length. Peak ankle dorsiflexion in stance and perhaps also in swing, and peak knee flexion in swing should increase. Peak plantar flexion moment in pre-swing phase may decrease. Based on the results of the pilot study by Lampire [15], we hypothesise that the length and lengthening velocity of the injected muscles will improve 1 month post injection.

We anticipate that these changes (particularly 1 month after BTX-A injection) will be associated with a concomitant increase in gait velocity during the 10-MWT and distance walked during the 6MWT, and reductions in performance time of the stairs and Timed Up and Go tests.

This is the first randomised, placebo-controlled trial using instrumented measures, such as 3D gait analysis and an isokinetic dynamometer, to evaluate the effects of BTX-A on gait parameters and force in patients with chronic stroke-related hemiparesis. We expect improvements of all the parameters studied in the BTX-A group. In contrast, we do not expect any significant improvement of any outcome measures in the placebo group.

Analysis of correlations between the different results will reveal if changes in the biomechanical properties of the injected muscles are related to improvements in kinematic and kinetic parameters and functional tests.

The results of this study will therefore increase understanding of the results of many previous un-controlled studies that have found improvements in kinematic parameters following BTX-A injection in patients with chronic hemiparesis.

## Abbreviations

10MWT: Ten meter walk test
6MWT: Six minute walk test
ABC scale: Activities balance confidence scale
ABILOCO: A measure of locomotion ability for adults
BBS scale: Berg balance scale
BTX A: Botulium toxin type A
EMG: Electromyography
GEE: Generalized estimation equation
MAS: Modified ashworth scale
MRC: Medical research council
MSM: Musculoskeletal models
RF: Rectus femoris
SKG: Stiff knee gait
ST: Stairs test
TA: Tibialis anterior
TS: Triceps surae
TUG: Timed up and go test
